**Starches:** Hetastarch (hydroxyethyl starch, HES) is produced by partial hydrolysis of amylopectin, which is made more soluble by the addition of glucose molecules. The 6% solution is the most commonly used solution (Hepaspan) and closely resembles 5% albumin; both are isotonic and increase the intravascular volume by the amount infused. The half life of hetastarch is longer (24 –36hours) than albumin15. It is both excreted by the kidneys and degraded by the enzymatic action of amylase. The major set back is that it alters haemostasis leading to increases in prothrombin time, partial thromboplastin time and bleeding time, and decreased levels of VIII:C and VIII:Ag18. As a result, the maximum daily dose recommended for adults is 1500mls/day and for children is 20mls/kg15. Pentastarch has a greater osmotic pressure and thus leads to greater volume expansion, nearly twice that of the volume infused. However, the half life is only 2.5 hours; 60% is excreted in the urine. Furthermore, Pentastarch is associated with similar haemostatic problems as Hetastarch. Allergic reactions are rare; < 0.1%.

**Gelatins:** The gelatins are produced from alkali-treated bovine collagen, which hydrolyses the esters and peptide links, followed by suspension in aqueous solution. There are two types of gelatins the succinylated gelatins (Gelofusin) or urea-linked gelatins (Haemacell). Both types of solutions are polydisperse. The small particles exert a large osmotic effect, but are then rapidly lost by glomerular filtration15,17. The volume expanding effect last for ~4 hours17. Compared to human albumin, the modified gelatins have similar shown efficacy in formal randomised trials19. Reports of haemostatic abnormalities after infusion of gelatins are rare and in vitro changes are related to dilution rather than a direct effect on the clotting cascade18. Allergic reactions are also rare < 0.1%. Haemacell has a higher calcium (6.26mmol/L) (which may lead to clotting if infused with blood) and higher potassium (5.1mmol/L) than Gelofusin15. Thus, the modified gelatins, in particular Gelofusin, emerge as the colloid with, theoretically, the least anticipated complication rate and for this study will be considered in this current study as the colloid of choice.

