**Theoretical considerations for the use of colloid in severe malaria**

Most of in-vivo trials examining the effect of different colloids on haemostasis (usually measure by blood loss) have been conducted in clinically stable patient groups undergoing corrective orthopaedic or cardiac surgery. In septic shock coagulation and haemostasis is disordered. In severe malaria bleeding secondary to disseminated intravasular coagulation (DIC)3 and procoagulant activity has been reported in adults with severe malaria20,21. In children whilst DIC is rarely encountered, little to no information exists on the abnormalities in coagulation and homeostasis22. There are however, a number of considerations when considering the use of non-albumin colloids. Firstly, in severe malaria moderate degree of thrombocytopenia is invariable22. In children admitted with severe malaria to KDH, thrombocytopenia (platelets counts < 150x1012) is common (>55%)23. Dextrans and starches are known to reduce von Willebrand factor and increase the risk of bleeding18. In the presence of thrombocytopenia, a von Willebrand-like syndrome is a possible complication. Albumin has no effect on coagulation and the effects by gelatins are mild, usually related to a dilutional effect18.

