**6. NULL HYPOTHESES.**

1. There is no difference in the safety profile or effect on physiological parameters of shock using gelatin-based colloids and albumin for the correction hypovolaemia in children with severe malaria.
2. The use of either of the two colloids will lead to no changes in coagulation after administration.

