### Secondary aims

1. To establish whether volume correction by Gelofusin can be undertaken safely and is comparable to albumin.
2. To examine whether the volume of Gelofusin required for correction of the physiological parameters of hypovolaemic shock is similar to albumin.
3. To establish whether albumin or Gelofusin lead to derangements of coagulation.

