**ii. Sampling procedure**

Eligible children will be randomised to receive either Gelofusin or 4.5% human albumin solution. Most children will receive 20-40mls over the first hour, dependant upon degree of acidosis and physiological improvements in shock. Otherwise, the management the children receive will be identical to our current standard of care. Two groups will be considered:

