#### Blood sampling and Laboratory procedures

Blood count, venous blood gases, blood sugar and chemistry (sodium, potassium and calcium) plasma creatinine, albumin, osmolality and red cell rheology will be measured at admission and 24hrs. Clotting and will be assessed at admission, 8 hours after colloid infusion and at 24 hours after admission (the details of the coagulation tests are covered in a separate proposal entitled ‘Investigation of coagulation activation in children with severe malaria’). Additional measurements of venous gas, plasma sodium, potassium, calcium, creatinine, albumin, red cell rheology and blood sugar will be taken at 8 hours to assess the response to volume resuscitation. Blood volumes taken for the purposes of monitoring are to be kept well within the maximum locally agreed volumes. In total 5mls of blood will be taken at admission (including all the standard blood tests) and an additional 2.5 mls the following 24 hours.

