**11. ETHICAL CONSIDERATIONS.**

i) Do no harm. These children will be closely monitored and fluid boluses given cautiously. Further fluid boluses would be withheld from children showing signs of cardiogenic shock or fluid overload.

ii) Blood samples would be required from all study children. However, the volumes of blood required would be minimized wherever possible and be kept well within the maximum locally agreed volumes (10 mls per patient over the period of the study).

iii) Informed consent will be sought from all families involved in the proposed studies (see attached consent form).

iv) Information pertaining to children involved in the proposed studies would be kept on secure password protected databases. In addition, personal data would be indexed using unique identification numbers rather than personal names.

v) The well being of the sick child is paramount. Therefore, at any time the supervising physician can override the requirements of the study if there were a clinical deterioration.

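### The coagulation hypothesis and aim are worded as effects of each colloid, but the design identifies only the Gelofusin–albumin difference, and a first post-infusion sample at 8 hours would probably miss an early dilutional effect

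*Protocol*

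**What the plan says.** Section 6, hypothesis 2: "The use of either of the two colloids will lead to no changes in coagulation after administration". Secondary aim 3 in section 7 has the same form: "To establish whether albumin or Gelofusin lead to derangements of coagulation". Hypothesis 1, directly above hypothesis 2, is worded as a difference between the two colloids.

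The design has two active arms (section 8c, Sampling procedure): "Eligible children will be randomised to receive either Gelofusin or 4.5% human albumin solution". There is no maintenance-only arm.

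The analysis text in section 9(b) lists abnormal clotting indices among the outcomes compared between interventions. It also says that the coagulation evidence will be weighed, with mortality, in judging the clinical safety of Gelofusin.

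On timing, section 8d (Blood sampling and Laboratory procedures) states: "Clotting and will be assessed at admission, 8 hours after colloid infusion and at 24 hours after admission". Section 4 (Choice of colloids) says of the gelatins: "The volume expanding effect last for ~4 hours", and puts their in-vitro clotting changes down to dilution. The later part of section 4 on theoretical considerations agrees: "the effects by gelatins are mild, usually related to a dilutional effect18" (the closing 18 is a reference number).

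The background is not consistent on albumin. Table one gives albumin and Gelofusin the same entry, a very mild dilutional effect on clotting. The theoretical considerations say that albumin does not affect coagulation at all.

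**The concern.** Hypothesis 2 and aim 3 are causal statements about each colloid, to be judged from change after infusion. Without a colloid-free arm, such a change mixes the colloid effect with whatever the disease and the rest of the treatment do over 24 hours. The protocol gives reason to expect movement: it describes disordered coagulation in septic shock, procoagulant activity in adults with severe malaria and frequent thrombocytopenia at this hospital, and says that hardly anything is known about coagulation in affected children. A change could be blamed on the colloid when it is the disease, and an absence of change could hide two effects that offset each other.

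The sampling times add a second limit. The one gelatin effect that the background leads the reader to expect is dilutional, and the first look after infusion comes at about twice the stated duration of volume expansion. A report of no change at 8 hours could be read as reassurance about the hours in which dilution would be greatest. Both problems bear on the advice about larger trials, because the coagulation results feed into the safety judgement on Gelofusin.

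**Working it through.** **There is no plan figure to reproduce.** The protocol gives no alpha, power, effect size or SD for coagulation and says that no formal sample size is calculated. The arm sizes agree: 2 acidosis groups × (20 + 20) = 80, so 40 per arm.

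**1. What the design identifies.** Let d be the mean change due to disease and other treatment, g the effect of Gelofusin and a the effect of albumin.

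- Change in the Gelofusin arm: d + g
- Change in the albumin arm: d + a
- Difference between arms: (d + g) − (d + a) = g − a

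Hypothesis 2 claims g = 0 and a = 0. The data yield d + g, d + a and g − a, and d is unknown. Only g − a is free of d. If albumin has no effect (theoretical considerations), a = 0 and the difference equals g. If both colloids have the same dilutional effect (Table one), g = a and the difference is zero although neither effect is. The two statements therefore decide whether albumin can serve as a no-effect reference.

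**2. Cost of testing hypothesis 2 as worded.** Assumptions: two-sided alpha 0.05, normal approximation, n = 40 in an arm, no colloid effect, and natural drift δ in units of the SD of change. The values of δ are illustrative. The rejection probability within one arm is p = Φ(δ√40 − 1.96) + Φ(−δ√40 − 1.96). For at least one of two independent arms it is 1 − (1 − p)².

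| Drift δ | One arm | At least one arm |
|---|---|---|
| 0 | 5% | 10% |
| 0.2 | 24% | 43% |
| 0.3 | 48% | 72% |
| 0.5 | 89% | 99% |

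Drift common to both arms cancels in the between-arm contrast, which stays at 5%.

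**3. What the between-arm contrast can detect.** At an assumed 80% power the detectable difference is (1.96 + 0.84) × √(2/n): 0.63 SD with 40 per arm, and 0.89 SD with 20 per arm inside one acidosis group.

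**4. Timing.** The clotting samples are at admission, 8 hours after infusion and 24 hours after admission. Against about 4 hours of volume expansion, 8/4 = 2, and none is scheduled in the first 4 hours after infusion. The protocol gives no time course for clotting, so the decay below is assumed to be exponential, with fraction f left at 4 hours and f² left at 8 hours. The peak between-arm difference is 0.63 SD, which 40 per arm would detect with 80% power at its peak.

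| Left at 4 h | Left at 8 h | Power at 8 h |
|---|---|---|
| 50% | 25% | about 10% |
| 25% | 6% | about 4% |
| 10% | 1% | about 3% |

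Power here counts rejections in the true direction only, so it tends to 2.5% as the effect vanishes.

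**5. Blood volume.** Section 8d plans 5 + 2.5 = 7.5 ml. Section 11 sets a limit of "10 mls per patient over the period of the study". The difference is 2.5 ml, but the protocol does not say whether the 7.5 ml includes everything drawn for the linked coagulation study.

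**The case against.** The strongest reply is that the sound comparison is already planned. Section 9(b) compares abnormal clotting indices between the randomised interventions, and common drift cancels there. This stands. A reader might infer from hypothesis 2 that the trial cannot answer any coagulation question; the documents do not support that, since Gelofusin relative to albumin can be estimated at 8 and 24 hours. What remains is a hypothesis and an aim that ask for something else.

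A reader might also infer that any gelatin effect has gone by 8 hours. The documents do not say so. The 4-hour figure is for volume expansion, no duration is given for a clotting effect, and the protocol calls the effect usually, not always, dilutional. The linked study concerns coagulation and endothelial activation, for which 8 and 24 hours may be suitable. Further boluses after the first hour are possible, so the time from the last infusion may vary. The test details are in the linked proposal, which is not at hand. This too stands, and it limits the timing point to an early, transient, dilutional effect.

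Finally, this is a secondary aim in a pilot study, and the only numerical criterion for preferring Gelofusin is mortality (section 8c). That lowers the stakes but does not remove them, because section 9(b) names the coagulation evidence as part of the safety assessment.

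**Conclusion.** The point holds in a limited form. Hypothesis 2 and aim 3 state effects that two active arms cannot identify, and they do not match the between-arm comparison in section 9(b). The Gelofusin–albumin difference is identified; the absolute effect of each colloid, and above all any shared effect, is not. Whether albumin may stand as a no-effect reference is left open by two statements in section 4 that disagree.

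On timing, no clotting sample is planned between admission and 8 hours after infusion, so an early dilutional effect would probably be missed. That rests on the protocol's own account of mechanism and on volume expansion as a guide to its duration.

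The false-rejection rates of 24% to 89% and the power of about 10% or less at 8 hours depend on assumed drift and decay. They show what could happen and are not estimates for this trial. The primary comparison of shock resolution is unaffected.

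**What to change.** - **Wording.** Restate hypothesis 2 and aim 3 as no difference between Gelofusin and albumin in coagulation indices after infusion, in line with hypothesis 1 and section 9(b).
- **Analysis.** Compare each index between arms with adjustment for the admission value, which is already collected. Report within-arm changes descriptively, without attributing them to the colloid.
- **Background.** Reconcile Table one with the theoretical considerations on whether albumin affects clotting, and state what a zero difference between arms would then mean.
- **Conclusion.** Limit any statement of no change, or of coagulation safety, to effects present at 8 hours or later.
- **Optional.** Add a small clotting sample within about 4 hours of infusion and keep the 8-hour sample. First confirm that total blood volume, including the linked study, stays within the 10 ml limit.

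The first four changes cost only wording. The optional sample costs one extra small draw per child and depends on the volume check. Moving the 8-hour sample instead would lose the only clotting value between admission and 24 hours and part it from the other 8-hour blood tests, so adding is preferable to moving.

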##### 7. OBJECTIVES

**Primary Aim**

1. To establish, through prospective intervention studies, whether volume depletion (hypovolaemia) and acidosis complicating severe malaria can be safely corrected by volume replacement with Gelofusin.

### Secondary aims

1. To establish whether volume correction by Gelofusin can be undertaken safely and is comparable to albumin.
2. To examine whether the volume of Gelofusin required for correction of the physiological parameters of hypovolaemic shock is similar to albumin.
3. To establish whether albumin or Gelofusin lead to derangements of coagulation.

##### 8. DESIGN AND METHODOLOGY

**a) Study Site.**

The study is to be based on the high dependency unit at the Centre for Geographical Medicine (Coast) and Wellcome Trust Laboratories at Kilifi District Hospital (KDH), Kenya.

**b) Study Population**

Children > 3 months old with severe falciparum malaria will be considered.

## Inclusion criteria

Presence of a severity feature (impaired consciousness and/or deep breathing) plus the presence of metabolic acidosis (base excess <-8).

## Exclusion criteria

Children of families who decline consent will receive standard management only. Children with severe malaria anaemia (haemoglobin < 5g/dl). Children with CSF changes consistent with meningitis. Children with clinical features of pulmonary oedema (defined as clinical evidence presence of fine crepitations in both lungs plus oxygen saturations < 95%). Those with evidence of raised intracranial pressure (brain stem features of coning, systolic blood pressure >90% centile for age plus falling heart rate and/or papilloedema) or any conditions that may contraindicate the use of volume replacement e.g.: established renal failure or known congenital heart disease.

##### c. Sampling

1. **Sample size determination**

These are pilot studies designed primarily to examine the safety of Gelofusin in children with severe malaria complicated by acidosis. As Phase I studies they are designed to provide adequate data to justify progression to next phase ie: multicentre studies, but with the desire to avoid exposure of a large group of children to a therapeutic intervention for which there is no available data in severe malaria. The trial will therefore, provide important data on the volumes required of Gelofusin in achieving satisfactory improvements in haemodynamic features of shock such in a similar manner to that which has been previously observed in children given albumin9. Formal sample sizes will therefore not be calculated. We aim to recruit 80 children: 40 will have moderate acidosis and 40 will have severe acidosis. 20 children in each group will receive Gelofusin and 20 will receive albumin. Since we showed that the greatest benefit of albumin was in those with coma24, at least 50% of the children recruited will have coma. Gelofusin, would be used in preference to albumin in larger studies if mortality were 10% (confidence interval 7.5-12.5%) or less.

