## Design and results: We randomly assigned children with severe malaria and metabolic acidosis (base excess <-8) to treatment with either albumin or saline: patients with moderate acidosis (base excess between –8 and -15) received 20 ml/kg; and those with severe acidosis (base excess <-15) received 40 ml/kg. For ethical reasons, a control (maintenance only) group was only included for patients with moderate acidosis. 150 children were enrolled. There was no difference in the rate of resolution of acidosis between the groups; however, requirement for alternative treatments was significantly more common in the maintenance only control group (P =0.004). Overall, mortality was significantly lower in patients receiving albumin (2/56; 3.6%) than those treated with saline (11/61; 18%) (2= 6.1, P=0.01). The improved mortality was entirely confined to the children admitted in deep coma, where mortality was (1/21; 5%) in albumin recipients as compared with (11/24; 46%) in saline recipients (P =0.002). Only one child developed pulmonary oedema (in the saline group) (overall incidence <1%) and 10 (7%) of the 135 survivors had neurological sequelae. Prior to the study mortality in children with malaria and severe acidosis had been consistently documented at between 25-40%, hence the low rate in the albumin recipients (4%) is lower than any previously reported patients with similar severity of disease. Our finding that the beneficial effect of albumin was greatest in the comatose patients (5% in the albumin treated group) and that most of the deaths in the saline treated patients appeared to be neurological in origin, is consistent with the predicted physiological effects of albumin14.

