**b) Provisions for data verification and validation.**

Currently all data is directly entered in File-Maker Pro where most variables entered have dichotomous values only and the values for numerical fields are selected from a list. Initial and final diagnoses are also chosen from a list of common diagnoses. The programmes have been written to include logical and range checks and flags for the reduction of duplication errors. Appropriate information quality control procedures are already established. Children fulfilling the admission criteria for the study will be flagged by the computer to alert the admitting physician.

Descriptive statistics will be used to compare the clinical characteristics of the groups at baseline (admission), 30minutes, 1 hr, 4 hrs, 8 hrs, 12 hrs and at 24 hours, by intervention. The major outcomes of interest will be the resolution of clinical features of shock and major side effects or complications; development of abnormal clotting indices, pulmonary oedema and death (as dependant variables) between the different interventions (independent variables). The primary measure of this outcome will compare the proportions attaining level one goals for resuscitation in those receiving albumin and Gelofusin. Using ANOVA baseline (admission) haemodynamic parameters (heart rate, respiratory rate, oxygen saturation, mean blood pressure and coma score) will compared to those at 1 hr, 2 hours and 8 hours between the different intervention groups. For the purpose of analysis percentage mean change in the parameter will be used between the baseline and next time point.

Expected outcome: We have shown that albumin results in low mortality (< 5%), whilst saline was associated with an overall mortality ~20%, rising to 46% in those with coma. Historical control data from children with the same clinical criteria show mortality was between 30-50%, when volume expansion was not routine. If the dose response to Gelofusin is similar to albumin then assessment of the clinical safety of Gelofusin will take the above mortality data into consideration, as well as the evidence arising from the coagulation studies.

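### The 10% mortality threshold for preferring Gelofusin carries a confidence interval (7.5-12.5%) that 40 Gelofusin children cannot give; at an assumed 95% level, 4/40 deaths gives 2.8-23.7%

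*Protocol*

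**What the plan says.** The sample size paragraph in Protocol section 8.c describes a pilot: "Formal sample sizes will therefore not be calculated". It then fixes the numbers: "We aim to recruit 80 children: 40 will have moderate acidosis and 40 will have severe acidosis", and "20 children in each group will receive Gelofusin and 20 will receive albumin". That makes 20 + 20 = 40 children on Gelofusin and 40 on albumin.

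The paragraph closes with a threshold for the next stage: "Gelofusin, would be used in preference to albumin in larger studies if mortality were 10% (confidence interval 7.5-12.5%) or less". No confidence level, method or denominator is given for the interval, there or elsewhere in the protocol.

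Two other places bear on how the threshold will be read. The Background reports from the earlier randomised trial that "mortality was significantly lower in patients receiving albumin (2/56; 3.6%) than those treated with saline (11/61; 18"%). The expected-outcome paragraph in section 9(b) says that, if the dose response is similar to albumin, "assessment of the clinical safety of Gelofusin will take the above mortality data into consideration", together with the coagulation evidence.

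**The concern.** A band of plus or minus 2.5 points around 10% is very tight for an arm of 40, in which a single death moves the observed rate by 2.5 points. The figure is part of a stated decision threshold about deaths in children. It is the only numerical criterion in the protocol for preferring Gelofusin to albumin in later studies.

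An ethics committee, the data safety and monitoring board or the planners of the multicentre trials could take from it that an observed 10% pins mortality down to within a few points, and so separates Gelofusin clearly from the 18% seen with saline. If the true interval is several times wider, this study cannot support that reading.

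**Working it through.** **Inputs.** Gelofusin arm n = 40 and threshold 10%, so 4 deaths (section 8.c). Stated interval 7.5-12.5%, half-width 2.5 points (section 8.c). Earlier saline mortality 11/61 = 18% (Background). Confidence level: not stated, so 95% is assumed and lower levels are tried.

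**Step 1: try to reproduce 7.5-12.5%.** The exact (Clopper-Pearson) interval for 4/40 at level 1 − α runs from the α/2 quantile of Beta(4, 37) to the 1 − α/2 quantile of Beta(5, 36).

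| Confidence level | Exact interval for 4/40 |
|---|---|
| 95% | 2.8-23.7% |
| 90% | 3.5-21.4% |
| 80% | 4.4-19.0% |
| 68% | 5.3-17.2% |
| 50% | 6.4-15.2% |

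Every row is wider than the stated interval. Other methods at 95% do not reproduce it either: Wilson 4.0-23.1%, Wald 0.7-19.3%.

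Other denominators do not help. One acidosis group (2/20) gives an exact 95% interval of 1.2-31.7%, and all 80 children (8/80) give 4.4-18.8%. The nearest match is 8/80 at 50% confidence (exact 7.5-13.3%), but 50% is not a conventional level and only 40 children receive Gelofusin.

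**Step 2: what plus or minus 2.5 points means at n = 40.** The standard error is √(0.10 × 0.90 / 40) = 0.0474. Then 0.025 / 0.0474 = 0.527, and 2Φ(0.527) − 1 = 0.40. The stated band is about a 40% interval.

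**Step 3: the n that would give it.** n = z² p(1 − p) / d² = 1.96² × 0.09 / 0.025² = 553.2, so 554 Gelofusin children at 95% (about 600 by the exact method). That is about 14 times the planned arm. At 90%, 80% and 68% the figures are 390, 237 and 143, all far above 40.

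**Step 4: a possible origin.** 3/40 = 7.5% and 5/40 = 12.5%. The band is exactly 4 deaths plus or minus one.

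**Step 5: what the point threshold can do.** P(X ≤ 4) for X ~ Binomial(40, p):

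| True mortality | Probability of meeting the threshold |
|---|---|
| 5% | 0.95 |
| 10% | 0.63 |
| 15% | 0.26 |
| 18% | 0.13 |
| 20% | 0.08 |

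The threshold therefore discriminates to some degree, but an observed 4/40 has an exact 95% interval that still contains 18%.

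**The case against.** *This is a pilot with no formal sample size.* True, and the point asks for neither a calculation nor more children. The figure of 554 shows how far the printed precision is from the design; a reader might infer that the trial is too small for its purpose, but the protocol claims no formal sizing and that does not follow.

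*The confidence level is not stated.* This stands as a caveat: 95% is an assumption. The conclusion does not depend on it, because the exact interval is wider than printed at every level down to 50%.

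*The band may be a tolerance of one death either side of four.* This is plausible, and would make the defect one of labelling. The text nevertheless says "confidence interval 7.5-12.5"%. Even as a band of 3 to 5 deaths it would contain the result with probability only 0.57 if true mortality were 10%.

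*The threshold does not settle the choice of colloid alone.* This stands. A reader might infer from section 8.c that mortality by itself decides which colloid goes forward. Section 9(b) does not support that: dose response and coagulation evidence are also weighed, and the primary measure is attainment of the level one resuscitation goals.

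*The protocol nowhere says that mortality above 12.5% would be excluded.* Also true. A reader might take the parenthesis that way, but the text makes no such claim and sets no rule on the upper limit.

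*The 18% comparator is not matched to this trial.* Partly stands. All 11 earlier saline deaths were among 24 children in coma, and this trial plans at least 50% in coma. If those rates carried over (11/24 in coma, none otherwise), saline-like mortality at 50% coma would be 0.5 × 11/24 = 22.9%, and the threshold would be met with probability 0.03 rather than 0.13. That makes the threshold a better screen than the 18% figure suggests, but the 95% upper limit of 23.7% for 4/40 still just covers 22.9%.

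**Conclusion.** The stated interval is wrong as written. No standard method at a conventional confidence level gives 7.5-12.5% for 40 Gelofusin children, nor for 20 or 80. Assuming 95%, the exact interval for 4/40 spans about 21 points, against the 5 printed.

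The error is confined to the precision attached to one threshold. The 10% figure, the sample size, the conduct of the trial and the primary comparison are unaffected. It still needs correcting, because it sits in the only numerical criterion for preferring Gelofusin and overstates what the study can show about deaths.

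Two opposite overstatements should be avoided. The threshold is not worthless: a true rate of 18% would fail it with probability 0.87. Nor can it be said without qualification to screen out saline-like mortality, since a result of 4/40 remains compatible with 18%.

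**What to change.** In section 8.c, delete the parenthesis holding the interval and express the threshold as a count, for example: *at most 4 deaths in 40 Gelofusin children (10%; exact 95% CI 2.8-23.7%)*. If a tolerance of one death either side was intended, say so and do not call it a confidence interval.

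Add one sentence saying that meeting the threshold does not establish true mortality of 10% or lower and does not by itself exclude the 18% seen with saline in the earlier trial.

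Optionally, give the probabilities of meeting the threshold: 0.95, 0.63, 0.26 and 0.13 at true mortality of 5%, 10%, 15% and 18%.

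The cost is a sentence or two of text. The stated precision becomes less favourable; no extra patients or procedures are needed.
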